## **Safety monitoring plan**

We have extensive experience with all aspects of the endotoxin vs. placebo inflammatory challenge and have administered endotoxin dose 0.8 ng/kg in over 150 adult participants (20-65 y) with no evidence of adverse events (AEs). Other studies have found that endotoxin dose 0.8 ng/kg can be administered in older adult subjects with no adverse effects . However, a 2.5-fold increase in the endotoxin dose to 2.0 ng/kg results in greater increases in proinflammatory cytokines, fever responses, and hypotension in older adults (61-69 years) as compared to young adults (20-27 years, unpublished data).

Safety monitoring is actively conducted throughout the study with hourly questions about physical symptoms and monitoring of vital signs. In addition, participants undergo a phone interview 1 and 7 days after the experimental session, in which there is active querying about physical symptoms, and evaluation of depressive symptoms by the MADRS. Therefore, adverse events will be identified by continuous reporting, and reviewed by the Principal Investigator (MRI).

Participants are given a 24-hour telephone number for calling the physician should feelings of depression or suicidal thoughts emerge in the 7 days following the protocol. In the event that significant medical or psychiatric problems are encountered, the study blind will be broken so that appropriate medical treatment will be provided.

The Principal Investigator has also designated appropriately qualified personnel to periodically perform quality assurance checks during and after the study. Such monitoring provides the opportunity to evaluate the progress of the study and to obtain information about potential problems. The monitor will assure that data are accurate and in agreement with any paper source documentation used, verify that subjects' consent for study participation has been properly obtained and documented, confirm that research subjects entered into the study meet inclusion and exclusion criteria, verify that study procedures are being conducted according to the protocol guidelines, monitor review AEs and serious adverse events (SAEs), and assure that all essential documentation required by Good Clinical Practices (GCP) guidelines are appropriately filed. At the end of the study, the monitors will confirm that the site has the appropriate essential documents on file, and advise on storage of study records.

An independent Data and Safety Monitoring Board (DSMB) is scheduled to meet every 6 months for the duration of the study. The DSMB is blind to subjects' actual randomized group assignments but has the opportunity to request at any time that the blind be broken, if concerns arise from the blinded data. Ad hoc meetings will be convened if SAEs occur that are

considered at least possibly related to the study procedures. For any adverse event, the DMSB determines whether the event is related to experimental protocol if it occurred during the experimental protocol, or if it could be attributed to the protocol if it occurred during the 7-day follow-up.

## **Ethics**

### *Institutional Review Board Review,*

The study will be conducted under a protocol as reviewed by the UCLA IRB; the study is conducted by scientifically and medically qualified persons; the benefits of the study are in proportion to the risks; the rights and welfare of the subjects are respected; the physicians conducting the study ensure that the hazards do not outweigh the potential benefits; the results reported will be accurate; subjects give their informed consent and are competent to do so and not under duress; and all study staff comply with the ethical principles in 21 Code of Federal Regulations (CFR) Part 50 and the Belmont Principles.

### *Ethical Conduct of the Study*

This study is conducted in accordance with all applicable Federal human research protections requirements and the Belmont Principles of respect for persons, beneficence, and justice. The procedures set out in this study are designed to ensure that all study personnel abide by the principles of the ICH GCP Guideline and the Code of Federal Regulations (CFR). The PI confirms this by signing FDA Form 1572.

### *Confidentiality of Data and Subject Records*

To maintain subject confidentiality, all laboratory specimens, eCRFs, reports and other records are identified by a subject number only. Research and clinical records are stored in a locked cabinet. Only research staff, and other required regulatory representatives have access to the records. Subject information is not released without written permission.

### *Compensation for Participation*

Subjects are compensated for travel expenses and for time contributed to this research study in the form of cash. Compensation is provided at each subject visit and is detailed in the informed consent form.

#### *Written Informed Consent*

The informed consent process and documents were reviewed and approved by the IRB and prior to initiation of the study. The IRB approved the screening eligibility scripts and the verbal consenting process for the screening interview. The IRB also approved the written consent document that contained a full explanation of the possible risks, advantages, and alternate treatment options, and availability of treatment in the case of injury, in accordance with 21 CFR Part 50. The consent document indicates that by signature, the subject. A written informed consent document, in compliance with 21 CFR Part 50, 32 CFR Part 219, and the Belmont Principles, and HIPAA Authorization is signed by the subject before any study-related procedures are initiated for each subject. All potential subjects for the study are given a current copy of the Informed Consent Form to read. All aspects of the study and informed consent are explained in lay language to the subject by either the investigator, or a medically trained designee. Any subject who is unable to demonstrate understanding of the information contained in the informed consent will be excluded from study participation.

All study subjects are given a copy of the signed informed consent.

#### *Data Handling and Record Keeping*

Source documents include but are not limited to original documents, data and records such as interview data, questionnaire data, and laboratory results. Data are transcribed from source documentation directly into a statistical program (i.e., SPSS). Paper copies of interview and questionnaire are available. The transcribed data are consistent with the source documents or the discrepancies are explained with a note in the source document. All entries, corrections, and alterations are made by the investigator or other authorized study personnel.

#### *Subject Identification and Confidentiality*

Subjects are identified by unique study ID numbers, and all paper source documents use this a unique subject number. No personal identifier will be used in any publication or communication used to support this research study. The subject number is used if it becomes necessary to identify data specific to a single subject. Regulatory bodies, such as the IRB, are eligible to review research records related to this study as a part of their responsibility to protect human subjects in clinical research. Personal identifiers are removed from research records.

#### *Retention of Records*

The investigator is responsible for creating and/or maintaining all study documentation required by Title 21 Code of Federal Regulations (21CFR) Parts 50, 54, 56, and 312, ICH E6 section 8, as well as any other documentation defined in the protocol. Federal and local regulations require that the investigator retain a copy of all regulatory documents and records that support the data for this study for at least 5 years following the date on which the results of the investigation were submitted for scientific publication and/or reported on clinicaltrials.gov.

#### *Data Sharing Plan*

The study include data from older adults with and without insomnia. The final dataset will include self-reported demographic and behavioral data from interviews, behavioral tasks, laboratory data from blood samples that characterize cellular and genomic markers of inflammation. The final dataset is stripped of identifiers prior to release for sharing, but there remains the possibility of deductive disclosure of subjects with unusual characteristics. Thus, we will make the data and associated documentation available to users only under a data-sharing agreement that provides for: (1) a commitment to using the data only for research purposes and not to identify any individual participant; (2) a commitment to securing the data using appropriate computer technology; (3) a commitment to destroying or returning the data after analyses are completed; 4) complies with UCLA IRB protocols for protected health information of its members; and 5) commitment to testing of a priori hypotheses. The timing of sharing of data occurs no later than acceptance for publication of the main findings of this project.

## Statistical Methods

### *Sample size*

Data from several studies show that endotoxin induces increases in depressed mood as measured by the POMS with a moderate to large effects ( $d=.48$  to  $.85$ ). In addition, endotoxin induces an exaggerated increase in depressed mood in adults with modest sleep disturbance, as compared to those without sleep disturbance, with a large effect ( $d=.71$ ). Using these preliminary data, Monte Carlo simulations indicate that sample sizes ranging from 42 to 60 yield a minimum of 85% power ( $\alpha=.05$ , two-tailed) for within time comparisons of main effect of condition (i.e., endotoxin vs. placebo), main effect of group (i.e., insomnia vs. comparison controls), and the interaction of condition x group, assuming that the interaction effect in older adults is similar to effects previously reported in adults. Hence, a target sample size of  $n=60$  per condition (i.e., endotoxin, placebo) or  $n=60$  per group (i.e., insomnia, comparison control) achieves 85% power for main effect of condition, main effect of group, and their interaction. Omnibus linear mixed models LMM analysis of repeated measures of depressed mood (primary outcome) yield greater statistical power ( $>90\%$ ). In addition, oversampling of the comparison controls, per protocol, yields even greater statistical power for between comparisons of group (i.e., insomnia,  $n=60$ ; comparison control,  $n=100$ ) and condition (i.e., endotoxin,  $n=80$ ; placebo,  $n=80$ ), and within group (i.e., control).

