Endotoxin is a model of systemic inflammation that can be used to experimentally interrogate the role of inflammation to induce depressive symptoms. Endotoxin resembles a pathogen-induced, naturally occurring inflammatory immune response, which is driven by a complex interplay of various cytokines, all with distinct kinetics and locally differing concentrations. Injection of a single cytokine does not model this response as it does not target the inflammatory cascade. Likewise, acute laboratory-based stress can activate inflammation, but only induces modest inflammatory and depression responses, which are less robust than found with endotoxin.

Increasingly, depression is viewed along a continuum of affective responses that lead to symptom expression, as opposed to being a categorical, diagnostic construct, and endotoxin affects the two cardinal affective symptoms that constitute depression: depressed mood and anhedonia. Endotoxin induces increases in depressed mood (Profile of Mood States [POMS]>3), and these responses are nearly 2-fold greater and within the range of clinical severity in those with sleep disturbance. Similarly, endotoxin induces increases depressive symptoms as indexed by the Montgomery-Asberg Depression Rating Scale (MADRS > 7), indicating mild depression, and these responses are attenuated by pretreatment with the antidepressant citalopram^73. Anhedonia (i.e., the lack of pleasure) also increases in response to endotoxin. Finally, endotoxin administration induces acute changes in the activity of neural substrates that are linked to depression. For example, the dorsal anterior cingulate cortex (dACC) and its functional connectivity to other regions are recognized for their role in the pathophysiology of depression. Endotoxin induces increases in activity of the dACC, which are

correlated with increases in inflammatory cytokines and reports of depressed mood . Moreover, endotoxin administration also reduces neural activity in the ventral striatum, a reward-related neural region , and decreased ventral striatum activity mediates effects of endotoxin on increases in depressed mood .

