## **METHODS**

### **Trial Design**

This investigation is a randomized controlled trial to evaluate the effects of an acute inflammatory challenge in response to endotoxin (0.8 ng/kg body weight) vs. placebo over 12 hours in older adults with insomnia as compared to older adults without insomnia. One hundred sixty older adults (aged 60 to 80 years), who are free from current psychiatric illness and medical conditions (e.g., inflammatory disorders), will be entered into this placebo-controlled, randomized, double-blind, parallel arm (endotoxin vs. placebo) experimental challenge protocol. Of this sample, approximately 60 participants will fulfill DSM-5 criteria for an insomnia disorder. Given the feasibility and cost utility of recruiting comparison controls who do not have insomnia, 100 controls will be used. Furthermore, a larger group of comparison controls lends more statistical power for the overall study, as well as greater statistical power for secondary analyses related, for example, to sex differences in depressive and inflammatory responses in older adults. Within each group, randomized conditions of endotoxin vs. placebo will be balanced with a 1:1 randomization ratio. Three pre-entry classification variables will be used to balance participants between those with insomnia and comparison controls including age (age 60-70 vs. 71-80), sex, and body mass index (18-24.9 vs. 25–35 kg/m^2). We will also use these pre-treatment classification variables in a modified randomization procedure, the minimization method  to ensure that the endotoxin vs. placebo conditions in the study design are balanced. The minimization method is particularly useful when it is important to balance experimental groups on a larger number of covariates . In its most simple application, this method weighs each classification variable equally and seeks to achieve an overall balance of the levels of these variables across experimental conditions, rather than a balance within each stratum. In addition, we will measure possible moderators (i.e., severity/ duration of insomnia, prior depressive episodes) and examine their potential moderating roles.

Participants will provide written informed consent as approved by the UCLA (University of California, Los Angeles) Institutional Review Board, as further described in the section on

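### One sample size and one power (at least 85%) are stated for both main effects and the interaction; on the direct reading of d=.71, interaction power is about 49% at 60 per group and 58% in the planned design

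*Protocol*

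**What the plan says.** The Sample size section of the protocol cites two sets of effects on POMS depressed mood: d=.48 to .85 for endotoxin, and d=.71 for the larger endotoxin-induced increase in adults with modest sleep disturbance than in those without. From Monte Carlo simulation of comparisons at a single time, two-sided alpha .05, it reports that "sample sizes ranging from 42 to 60 yield a minimum of 85% power" for both main effects and the interaction, assuming that the interaction resembles the one seen earlier in adults. It concludes that 60 per condition, or 60 per group, "achieves 85% power for main effect of condition, main effect of group, and their interaction".

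Two further statements follow. "Omnibus linear mixed models LMM analysis of repeated measures of depressed mood (primary outcome) yield greater statistical power", given as above 90%. Oversampling controls to 100 is said to add power for the comparisons of group and of condition and within the control group; the interaction is not in that list.

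Under Trial Design, "approximately 60 participants will fulfill DSM-5 criteria for an insomnia disorder", with 100 controls and 1:1 allocation within each group. The planned cells are therefore 30/30 (insomnia) and 50/50 (controls).

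**The concern.** The trial's hypothesis is that insomnia heightens the response to endotoxin, which is the condition-by-group interaction. The Statistical analysis section lists it among the key results.

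An interaction contrast combines four cell means. In equal cells, on a common SD scale, its standard error is twice that of a main effect. One n and one power can serve all three tests only if the interaction effect is about twice as large as the main effects, and the cited effect sizes do not say so.

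If power for the interaction is nearer 50–60% than 85%, a non-significant result is quite likely even when the assumed effect is real. A reader who relies on the stated figure would put the chance of missing it at no more than 15%.

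**Working it through.** **Inputs.** Two-sided alpha .05; d=.71 for the interaction; d=.48 to .85 for endotoxin; 60 per group or condition (30 per cell); planned cells 30/30/50/50. All are from the Sample size and Trial Design sections. Outcome SD is set to 1, at a single time, with no covariate adjustment.

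**Formulas.** Interaction: SE = sqrt(sum of 1/n over the four cells). Simple two-group contrast: SE = sqrt(1/n1 + 1/n2). Power is from the noncentral t with noncentrality d/SE; the normal approximation is Phi(d/SE − 1.96).

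**Trying to reproduce 85% for the interaction, with d=.71 as a difference of differences**
- 60 per group, 30 per cell (where the 85% is stated): SE = sqrt(4/30) = 0.365; .71/0.365 = 1.94; power 48.7% (normal 49.4%).
- Planned 30/30/50/50: SE = sqrt(2/30 + 2/50) = 0.327; .71/0.327 = 2.17; power 57.9% (normal 58.5%).
- 60 per cell (N=240): SE = sqrt(4/60) = 0.258; .71/0.258 = 2.75; power 78.2%.
- For 85% at .71 SD: 72 per cell, 288 in total.
- Detectable at 85% with 30/30/50/50: (1.96 + 1.036) × 0.327 = 0.98 SD.

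**Other readings of d=.71**
- Converted from an interaction test (d = 2f): the difference of differences is 2 × .71 = 1.42 SD. Power is 97.1% at 30 per cell and 99.1% at 30/30/50/50.
- Insomnia vs control among endotoxin recipients only, 30 vs 50: SE = sqrt(1/30 + 1/50) = 0.231; power 85.9%. This is the closest match to 85% found without covariate adjustment, but it is a simple contrast and not the interaction.
- Baseline adjustment with correlation r, d on the raw-score SD, so d/sqrt(1 − r²): at 30/30/50/50, r=.5 gives 70–71% and r=.7 gives 86%. At 30 per cell, r=.7 gives 77–78%. No r is stated.

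**Which reading fits the protocol's own figures?** As a plausibility check, take .48 to .85 as the response without sleep disturbance. A difference of .71 makes the response with sleep disturbance (.48 + .71)/.48 = 2.5 to (.85 + .71)/.85 = 1.8 times as large. A difference of 1.42 makes it (.48 + 1.42)/.48 = 4.0 to (.85 + 1.42)/.85 = 2.7 times as large. The background section says "these responses are nearly 2-fold greater and within the range of clinical severity in those with sleep disturbance". The figures come from different studies, so this supports the direct reading without proving it.

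**Main effect of condition**
- d=.48, 60 vs 60: SE = sqrt(2/60) = 0.183; power 74.1% (normal 74.8%). 85% needs 79 per condition.
- d=.48, simple 80 vs 80: SE = sqrt(2/80) = 0.158; power 85.5%.
- d=.48, condition effect weighted equally over the two groups in 30/30/50/50: SE = 0.327/2 = 0.163; power 83.2%.
- d=.71 and d=.85, 60 vs 60: 97.1% and 99.6%.

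**The case against.** The strongest reply is that d=.71 is not defined. The section gives no contrast, standardiser or SD, and the cited study is not at hand. The text assumes an interaction similar to one already reported, which is compatible with an effect size converted from an interaction test. On that scale the claim of at least 85% is met. The figure also comes from a simulation whose inputs are not shown and may be recorded elsewhere, and a baseline correlation of about .7 would bring the planned design to 86%. All of this stands, so the 49% and 58% must be given as conditional.

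Four stronger conclusions are tempting, and the protocol does not support them:
- That the 85% is wrong outright. It fails on the direct reading, but the scale of d is open.
- That the protocol claims 85% for the interaction at 30/30/50/50. It attaches the figure to 60 per condition or per group. The matching recalculation is 49%; the 58% describes the planned design.
- That the claim of more than 90% for the mixed model is refuted. That power depends on within-person correlation, time course and contrast, and some plausible choices exceed 90%.
- That the near-doubling in the background section fixes a still lower power. That would combine one study's ratio with other studies' main effects, and would need to assume how sleep disturbance was distributed in them.

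It can also be said that the low-end d=.48 may not have been the simulation input. That is possible, but the section cites the whole range as its basis and then states a minimum.

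**Conclusion.** The statement that 60 per condition or per group gives at least 85% for both main effects and the interaction does not follow from the inputs printed beside it.

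On the direct reading of d=.71, interaction power is about 49% at the stated size and about 58% in the planned design, and N=160 reaches 85% only for about 0.98 SD. These figures assume a single time point, equal variances, no covariate adjustment and two-sided alpha .05. The claim is rescued only by a 1.42 SD interaction, which sits poorly with endotoxin effects of .48 to .85, or, at N=160, by strong adjustment that the section does not mention.

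The main-effect shortfall does not depend on how .71 is read: d=.48 gives 74% at 60 per condition. The planned 160 largely repairs this (83–85%).

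This is a fault in a stated power figure for the central hypothesis. It does not show that the design is unusable.

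**What to change.** Keep N=160 and revise the Sample size section.

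- State the assumed interaction as a difference of differences in SD units, and say which SD.
- Replace the 85% interaction claim with conditional figures: about 58% at .71 SD and 85% at 0.98 SD, for 30/30/50/50, one time point, no covariate adjustment. Alternatively, re-run the simulation and state its inputs.
- Restate the condition main effect at d=.48 as about 83% (weighted equally over the two groups) to 85% (simple 80 vs 80).
- Keep the figure above 90% for the mixed model only if it is tied to a named contrast with a stated within-person correlation and time course.
- Commit to reporting the interaction with its confidence interval, and to not reading a non-significant result as absence of moderation.

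The cost is a less favourable stated power, some rewording and one simulation. No participants are added, and allocation, outcomes and planned models stay as they are.

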### *Statistical analysis*

Analyses will be reported according to the CONSORT statement, and will use Intent-To-Treat samples (i.e., all persons who were randomized and received either endotoxin or placebo will be included in the analysis). Measured baseline and outcome variables will be assessed for distributional qualities and transformed if necessary for use in the selected statistical models. All pre-classification variables, including age (60-70 years vs. 71-80 years), sex, and body mass

index (18-24.9 vs. 25–35 kg/m^2), as well as other baseline values will be compared between healthy controls and insomnia patients; those having a relationship with the outcome variables will be considered for inclusion as covariates in the main analyses. The detailed statistical analysis plan will be reviewed by the independent Trial Data Monitoring and Steering Committees of the UCLA Clinical Translational Sciences Institute. IBM SPSS Version 28, SAS version 9.4 or other established statistical packages will be used for all analyses.

The basic design is a 2 group (insomnia vs. comparison controls) by 2 condition (endotoxin vs. placebo), analysis variance (ANOVA) with one or more repeated measures of outcome analyzed with linear mixed models (LMM). LMM provides unbiased estimates when observations are missing at random. The timing repeated measures varies by assessment as noted above. The key results are the main effects of group, condition, and their interaction; for those analyses with repeated measures, the two main effects and interaction will further interact with the time variable.

*Primary Outcome: Depressed Mood.* The primary outcome is tested with LMM for the depressed mood subscale of the POMS and for severity of depressed mood and depressive symptoms of the MADRS with a time frame up to 12 hours.

*Secondary Outcome: Depressive Symptoms.* Change in depressive symptoms is tested with LMM for the clinician-rated assessment of depressive symptom severity as measured Hamilton Rating Scale for Depression with a time frame up to 8 hours.

*Secondary Outcome: Negative Affective Responding.* Change in negative affective responding is tested with LMM for the following behavioral tasks, Emotion Recognition Task and Emotion Intensity Task with a time frame of about 2 hours. Similar analytic strategy will be

applied for other secondary outcomes related to negative affect responding with time frames ranging from 4- to 12 hours.

*Secondary Outcome: Positive Affective Responding.* Change in positive affective responding is tested with LMM for the following behavioral tasks, reward learning (i.e., PRT) and reward motivation and sensitivity to monetary reward (EEfRT) with a time frame of about 2 hours

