Additional exclusion criteria are: current and regular use of prescription medications such as steroids, non-steroid anti-inflammatory drugs, aspirin, immune-modifying drugs, opioid analgesics, statins, antihypertensive or other cardiovascular drugs (i.e., antiarrhythmic, antianginal, and anticoagulant drugs); antidepressant medications or other psychotropic medication in the last 6 months; current smoking or excessive caffeine use (>600 mg/day) because of the known effects on proinflammatory cytokine levels ; history of recreational drug use in last 6 months or evidence of such use as determined by screening urine test for substances; body mass index > 35 kg/m^2 because of the effects of obesity on proinflammatory cytokine activity  and also on risk for sleep disordered breathing; any clinically significant abnormalities on laboratory tests; clinically significant abnormalities in electrocardiogram; and evidence of cognitive impairment with scores on Mini-Mental Status Examination 24 or less. On the day of the experimental protocol, participants will be excluded should they show any of the following physical signs: blood pressure less than 90/60 or greater than 160/120 mmHG, pulse less than 50 beats/minute, or temperature greater than 99.5°F.

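### Age and BMI are named as candidate covariates in two classes each; entering the measured values would control the non-randomised insomnia contrast better, at almost no cost

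*Protocol*

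**What the plan says.** Three statements in the protocol bear on this.

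- **Trial Design.** "Three pre-entry classification variables will be used to balance participants between those with insomnia and comparison controls", namely age (60-70 vs 71-80), sex and BMI (18-24.9 vs 25-35 kg/m²). The same classes feed the minimisation of endotoxin vs placebo, which "seeks to achieve an overall balance of the levels of these variables across experimental conditions, rather than a balance within each stratum".
- **Statistical analysis.** The covariate rule opens with "All pre-classification variables, including age (60-70 years vs. 71-80 years), sex, and body mass" index, with the same BMI cut. It continues "as well as other baseline values will be compared between healthy controls and insomnia patients". Variables related to the outcomes are then to be considered as covariates in the main analyses. The same section makes the effects of group, condition and their interaction the key results.
- **Eligibility Criteria.** Participants are aged 60 to 80. BMI above 35 kg/m² is excluded, in part "because of the effects of obesity on proinflammatory cytokine activity".

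Only endotoxin vs placebo is randomised, stratified by insomnia status (Trial Design). Height and weight are taken to calculate BMI (Trial Procedures, baseline eligibility), so a measured BMI exists for everyone. Exact age is needed for eligibility.

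**The concern.** Two groups can agree on the share aged 60-70 and the share with BMI below 25 and still differ in age or BMI inside those classes. For endotoxin vs placebo this is chance imbalance, which randomisation covers. For insomnia vs control it is possible confounding, and restriction by eligibility and balancing on classes control it only in part.

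The protocol gives its own reasons why both variables matter. The Background links usual aging to inflammation, and the eligibility section links obesity to cytokine activity. The upper BMI class runs from 25 to the exclusion limit of 35.

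At stake are some residual confounding in the group effect on mood and cytokines, some in the interaction under a further condition, and a loss of precision, because a class explains less outcome variance than the measured value. The covariates also carry over to the mediation models, which are to use the covariate set of the mixed models (Pre-specified secondary analyses).

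**Working it through.** The protocol states no figure on this point, so there is none to reproduce.

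**Inputs.** From the protocol: age 60 to 80, cut between 70 and 71; BMI 18 to 35, cut at 25. Assumed: the shape of each distribution. Age in completed years is treated as running from 60 to just under 81.

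**Variance left within classes.** With p the proportion in the upper class and m the class means:

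share left = 1 − p(1−p)(m_high − m_low)² / Var(x)

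*Uniform values.* The class means differ by half the range and the variance is range²/12, so the share kept is 3p(1−p).
- Age: p = 10/21 = 0.476; 3 × 0.476 × 0.524 = 0.748; about 25% left.
- BMI: p = 10/17 = 0.588; 3 × 0.588 × 0.412 = 0.727; about 27% left.

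*Normal values cut at the median.* 1 − 2/π = 36.3% left.

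*Truncated normal, one case in full: BMI mean 27, SD 4, limits 18 and 35.* The limits and the cut are −2.25, −0.5 and 2 SDs from the mean.
- Upper class: p = 0.6687/0.9650 = 0.693
- m_low = 27 − 4 × (0.3521 − 0.0317)/0.2963 = 22.67
- m_high = 27 + 4 × (0.3521 − 0.0540)/0.6687 = 28.78
- Var = 16 × 0.8136 = 13.02
- Share kept = 0.693 × 0.307 × 6.11² / 13.02 = 0.61; 39% left

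Other truncated-normal cases, by simulation with the protocol's cuts:

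| Variable | Assumed mean, SD | Share in upper class | Variance left |
|---|---|---|---|
| Age | 70, 8 | 45% | 29% |
| Age | 70, 5 | 42% | 34% |
| Age | 68, 5 | 29% | 38% |
| Age | 67, 5 | 23% | 42% |
| Age | 66, 5 | 18% | 46% |
| Age | 65, 5 | 14% | 51% |
| Age | 62, 5 | 6% | 66% |
| BMI | 25, 4 | 52% | 33% |
| BMI | 26, 4 | 61% | 36% |
| BMI | 27, 4 | 69% | 39% |
| BMI | 28, 4 | 77% | 44% |
| BMI | 29, 4 | 83% | 50% |

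The share rises as the sample falls mostly into one class.

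**Group difference left after adjusting for the class.** One group's covariate distribution was shifted and the covariate regressed on group and class.

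| Variable | Assumed mean, SD | Difference before | Difference after | Left |
|---|---|---|---|---|
| Age | 67, 5 | 1.51 years | 0.59 | 39% |
| Age | 70, 5 | 1.60 years | 0.52 | 32% |
| Age | 70, 8 | 1.79 years | 0.51 | 28% |
| BMI | 25, 4 | 1.22 | 0.42 | 35% |
| BMI | 26, 4 | 1.20 | 0.46 | 38% |
| BMI | 27, 4 | 1.19 | 0.50 | 42% |

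These runs let the class shares differ between groups. If recruitment has already balanced the classes exactly, whatever difference remains lies within classes, and a class term removes none of it.

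**From covariate difference to bias.** Let δ be the group difference within classes, and γE and γP the outcome slopes per unit under endotoxin and placebo. Condition is randomised within group, so δ is the same in both conditions in expectation. Then:
- bias in the group effect = δ × (γE + γP)/2
- bias in group by condition = δ × (γE − γP)
- bias in the condition effect = 0 in expectation

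The protocol gives no value for δ, γE or γP, so none of these can be put on the POMS, MADRS or cytokine scale. With a correctly specified linear term for the measured value, the part left by the adjustment is 0%.

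**The case against.** The strongest reply is that covariate form belongs in the statistical analysis plan, which the protocol announces and which is not at hand. The parentheses may only identify the classification variables. The same sentence admits other baseline values, and the sentence before it speaks of checking distributions and transforming, which suits continuous variables. Nothing forbids a continuous term. Restriction by age and BMI and balancing on the classes already give partial control.

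Much of this stands. A reader might infer that the protocol allows age and BMI only as two classes, or that nothing protects the insomnia contrast. The text supports neither. A reader might also take the percentages as the fraction of confounding left in the results. They are shares of covariate variance under assumed distributions, and bias needs δ and a slope as well. Nor does the 40% weight span of the upper BMI class at equal height (35/25 = 1.40) show that the groups differ within it.

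What does not stand is the claim that the protocol is silent. It writes the two-class form into its analysis section and names no other form for these variables. A better form is available from data already collected, so this is more than missing detail.

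The objection is also right about adding products with condition to every model. Effects already interact with time over up to 12 hours of repeated measures in 160 participants, so those products are a debatable trade-off and not a free improvement.

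**Conclusion.** The point holds as a minor, nearly free improvement. The named form of the age and BMI covariates is weaker than it need be for the one contrast that randomisation does not protect. The classes leave about 25-27% of covariate variance uncontrolled if values are uniform, about 33-45% in most of the roughly normal cases, and up to 66% in the most lopsided case tabulated. These figures rest on assumed distributions.

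The consequence for the results is conditional. The group effect is affected if the groups differ within classes and the variable relates to the outcome. The interaction is affected only if the variable also modifies the response to endotoxin. The endotoxin vs placebo comparison is not at risk.

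**What to change.** Keep the two-level classes for balancing the groups and for minimisation. In Statistical analysis, add one sentence stating that age and BMI enter the models as measured, continuous covariates. Use their products with condition only as a sensitivity analysis of the group by condition effect.

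No new data are needed. The cost is that sentence and about two degrees of freedom in the main model compared with a model without age and BMI; compared with a model holding the two class terms, linear terms cost none.
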